### Outcomes and definitions {12}

Primary outcome is the hypoxemia incidence, defined as SpO_2_ < 90% for > 10 consecutive seconds during the procedure [18]. Timing begins at first SpO_2_ reading < 90% and continues until resolution.

Secondary outcomes are as follows:Severe hypoxemia incidence, defined as SpO₂ ≤ 75% for any duration or SpO₂ ≤ 90% for ≥ 60 consecutive seconds or longer during the procedure [17].Hypoxemia duration, defined as total cumulative time (seconds, mean [SD]/median [IQR]) with SpO₂ < 90% during procedure.Emergency airway intervention, defined as requiring jaw thrust maneuver, mask-assisted ventilation with procedure interruption, tracheal intubation during procedure and in PACU.Hypotension incidence defined as MAP decrease ≥ 20% compared with baseline (average of 3 pre-procedure readings) during procedure and in PACU.Involuntary body movements are defined as any limb/trunk movements requiring physical restraint or procedure interruption during the procedure.Total propofol dose defined as cumulative amount (mg, mean [SD]/median [IQR]) administered during procedure.Length of procedure (minutes, mean [SD]/median [IQR]) defined as the time quantum from gastroscope insertion to complete withdrawal.Recovery time (minutes, mean [SD]/median [IQR]) defined as the time quantum from scope removal to achieving MOAA/S score of 5 or responsive to normal voice.Clinician satisfaction measured via 10-cm VAS immediately post-procedure (0 = extremely dissatisfied, 10 = completely satisfied) after the procedure.AEs will be documented and assessed continuously during the procedure and in the PACU. Occurrence counts and severity (where applicable) will be documented in the CRFs as follows:Cough: Defined as ≥2 consecutive coughs during the procedure or in the PACU; assessed by direct observation and recorded as presence/absence.Hiccups: Defined as ≥2 episodes within 1 minute; recorded as presence/absence during the procedure or in the PACU.Nausea/vomiting: Graded on a 3-point severity scale (1=mild/nausea only, 2=moderate/transient vomiting, 3=severe/prolonged vomiting) and assessed both during the procedure and in the PACU.Reflux/aspiration: Defined as visible gastric content in the oropharynx or airway; recorded as presence/absence during the procedure.Laryngospasm: Defined as complete airway obstruction with no airflow despite respiratory effort; assessed by auscultation and waveform capnography, and recorded as presence/absence during the procedure.

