### Sample size {14}

All calculations were performed using PASS 15.0 (NCSS, LLC), with parameters verified by an independent statistician. The sample size calculation was based on detecting a clinically meaningful difference in the primary outcome of hypoxemia incidence (SpO_2_ < 90% for > 10 s) between study groups. From our pilot data, we anticipate a 50% incidence of hypoxemia in the control group receiving standard propofol sedation. We hypothesize that low-dose esketamine will achieve an absolute risk reduction of 15%, corresponding to a 35% hypoxemia incidence in the intervention group. Using a one-tailed *Z*-test for proportions (unpooled) with 80% power (*β* = 0.20) and a significance level of *α* = 0.025 (selected because esketamine’s established respiratory safety profile makes increased hypoxemia biologically implausible; detecting non-inferiority/superiority is the sole clinical priority.), we calculated a minimum requirement of 132 participants per group. To account for potential 10% attrition, we will enroll 147 participants per group (*N* = 294 total). This conservative approach ensures adequate power even if the actual control group incidence varies between 45 and 55% or if dropout rates reach 15%. The one-tailed design is appropriate given esketamine's established respiratory safety profile and the clinical irrelevance of detecting increased hypoxemia risk with this intervention.

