## Statistical methods

### Statistical methods for primary and secondary outcomes {20a}

All analyses will be conducted using SPSS 23.0 (IBM Corp) by a statistician blinded to group allocation. The primary outcome will be analyzed using a one-sided *Z*-test at *α* = 0.025, while secondary outcomes will employ two-sided tests with *α* = 0.05.

Continuous variables will be assessed using the Kolmogorov–Smirnov test examining for normality. Normally distributed data will be presented as mean ± standard deviation (SD). Non-normal data will be presented as median or interquartile range (IQR). Categorical variables will be presented as counts and percentages.

For the primary outcome of hypoxemia incidence, we will employ a one-sided Z-test for proportions to evaluate the hypothesized reduction in the esketamine group, reporting absolute risk differences with 95% confidence intervals. Secondary outcomes will be analyzed using appropriate statistical tests based on variable characteristics: continuous normally distributed variables will be compared using independent *t*-tests, while non-normal continuous data will be assessed with Mann–Whitney *U* tests. Categorical outcomes will be analyzed using *χ*^2^ tests or Fisher’s exact tests as warranted by sample sizes. For time-to-event outcomes such as duration of hypoxemic episodes, we will utilize Kaplan–Meier survival analysis with log-rank tests. Longitudinal physiological measurements including mean arterial pressure and heart rate will be evaluated using repeated measures ANOVA, with post hoc Bonferroni corrections applied to account for multiple comparisons while maintaining the overall type I error rate at *α* = 0.05. All comparative analyses will be conducted by a blinded statistician using SPSS version 23.0, with two-sided tests (*α* = 0.05) employed for all secondary outcomes to conservatively assess potential group differences.

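### Hypoxemia duration is defined as a per-patient total with many zeros, but is assigned a Kaplan–Meier/log-rank analysis that does not fit that definition

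*Protocol article*

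**What the plan says.** Outcomes and definitions {12} lists as a secondary outcome "Hypoxemia duration, defined as total cumulative time" with SpO2 below 90% during the procedure, in seconds, to be summarised by mean and SD or median and IQR. That is one continuous value per patient.

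Statistical methods {20a} gives a general rule for continuous outcomes: t-tests if normal, "while non-normal continuous data will be assessed with Mann–Whitney" U tests otherwise. It then takes duration out of that rule: "For time-to-event outcomes such as duration of hypoxemic episodes, we will utilize Kaplan–Meier survival analysis with log-rank tests". That sentence does not say how patients without an episode enter, how several episodes in one patient are combined, or what would be censored. The same section says that all randomised participants are analysed by intention to treat.

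The primary event is SpO2 below 90% "for > 10 consecutive seconds during the procedure". Sample size {14} plans on this: "we anticipate a 50% incidence of hypoxemia in the control group", with a 15-point reduction "corresponding to a 35% hypoxemia incidence in the intervention group".

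**The concern.** The two sections describe different quantities. {12} has a total per patient, observed over a fixed window. {20a} has the length of an episode, treated as a waiting time. Only a patient who desaturates has an episode whose end can be timed, so the survival formulation has no natural place for the patients who did best.

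This leaves two ways to carry out the sentence. One drops the patients without an episode and compares groups formed after randomisation by something close to the primary outcome. The other enters them as events at time 0. They then leave the risk set at once, and every later log-rank term compares hypoxemic patients only.

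The Discussion names the combination of incidence and duration metrics as a strength of the design, so a duration result that misses a benefit or points the wrong way would be read alongside the primary result.

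**Working it through.** The protocol gives no figure for the duration analysis, so there is none to reproduce.

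**1. Share of zeros.** Inputs from {14}: 147 per group, incidence 50% and 35%.
- Patients with a qualifying event: 147 × 0.50 + 147 × 0.35 = 73.5 + 51.45 ≈ 125; 125/294 = 42.5%.
- Patients without one: 50% of controls, 65% of the esketamine group, (50 + 65)/2 = 57.5% overall.
- {14} also considers what happens "if the actual control group incidence varies between 45 and 55" per cent. With the same 15-point reduction, the overall share is 1 − (0.45 + 0.30)/2 = 62.5% down to 1 − (0.55 + 0.40)/2 = 52.5%.
- With the 26–85% incidence range in the Discussion as control rates, it runs from 1 − (0.26 + 0.11)/2 = 81.5% to 1 − (0.85 + 0.70)/2 = 22.5%.

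The primary event needs more than 10 s, while duration counts any time below 90%. A patient with only brief dips has no event but a non-zero duration. At given rates, these shares are therefore upper bounds for zeros, and 125 is a lower bound for patients with any time below 90%.

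**2. Hypoxemic patients only: how a reversal can arise.** The documents give no durations, so these are assumed. Per 100 controls, 25 have 20 s and 25 have 60 s. Esketamine prevents 15 of the 50 cases.

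| Cases prevented | Mean among hypoxemic patients | Mean over all 100 |
|---|---|---|
| Control (none) | (25×20 + 25×60)/50 = 40 s | 2000/100 = 20 s |
| 15 short | (10×20 + 25×60)/35 = 48.6 s | 1700/100 = 17 s |
| 7.5 short, 7.5 long | (17.5×20 + 17.5×60)/35 = 40 s | 1400/100 = 14 s |
| 15 long | (25×20 + 10×60)/35 = 31.4 s | 1100/100 = 11 s |

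Nobody is worse off in any row, and the all-patient mean always falls. The mean among hypoxemic patients rises, stays or falls according to which cases are prevented.

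**3. Simulation of both readings.** 147 per group, two-sided 0.05. Zeros follow the stated incidences; non-zero durations are assumed lognormal (median 30 s, log-SD 0.7). There were 1500 runs per no-effect row and 800 per other row, so the Monte Carlo standard error is at most √(0.25/800) ≈ 1.8 points.

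| Scenario | Log-rank, all, zeros at time 0 | Log-rank, hypoxemic only | Mann–Whitney, all |
|---|---|---|---|
| No effect, 50% in both | 6.2% | 5.4% | 5.4% |
| No effect, 35% in both | 5.0% | 5.3% | 4.5% |
| 50% vs 35%, same lengths | 37% | 4% | 70% |
| Shortest 30% of episodes prevented (50% → 35%) | 6% | 38% find esketamine longer | 34% |

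In the last row the median among hypoxemic patients is about 39 s with esketamine and 31 s with control, although no patient's duration was lengthened.

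All three tests use only the ordering of the durations. The assumed median and spread therefore affect the rejection rates only through ties from rounding to whole seconds. The assumption that matters is which episodes the drug prevents.

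**The case against.** **No restriction is stated.** A reader might infer that the protocol limits the log-rank test to hypoxemic patients and that the analysis is therefore invalid. The documents do not support that. Nothing in {20a} restricts the test, and its intention-to-treat statement points the other way. With everyone included, the simulated type I error is 5–6%. This objection stands: the selection bias is conditional on one reading, and under the other the loss is in power and interpretability.

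**Zeros need not be the majority.** A reader might also infer that most patients have zero duration. On the planning rates 57.5% is an upper bound, it is exactly 50% in controls, and the share could be far lower near the top of the incidence range in the Discussion. This stands too, but the argument needs only a large share.

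**The reversal is constructed.** The 20 s and 60 s values, and a drug that prevents only short episodes, are not in the documents. The example shows that a reversal is possible, not that it is likely.

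**Censoring could occur.** {12} starts timing at the first reading below 90% and runs it to resolution, and {10} withdraws patients for intubation, an incomplete procedure or one over 15 minutes. An episode might therefore be cut off. That applies to episode length. A total confined to the procedure is known when monitoring of the procedure ends, so it does not rescue the method for the outcome as defined.

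**Only one test is assigned.** The specific sentence on duration would ordinarily override the general rule. This is fair: the defect is the choice of method, not a double assignment.

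**Conclusion.** The point holds as a mismatch between a stated outcome and a stated method. It is not a detail left to the analysis plan. Neither way of carrying out the sentence estimates the difference in cumulative seconds between the randomised groups.

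- Restricted to patients with an episode, the test rests on about 125 of 294 patients with a qualifying event, conditions on what treatment is meant to change, conflicts with intention to treat, and can reverse direction if short episodes are preferentially prevented.
- With all patients included, its size is near nominal, but in the equal-length scenario its power is about 37% against about 70% for Mann–Whitney.

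The zero shares rest on the planning rates, and the power and reversal figures on assumed durations. This is one secondary outcome, so the primary conclusion is untouched. The change should still be made, because the better method is already in the protocol.

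**What to change.** In {20a}, delete the Kaplan–Meier/log-rank sentence for hypoxemia duration. State that cumulative seconds with SpO2 below 90% are compared in all randomised patients, with 0 for those who never desaturate, by the existing Mann–Whitney rule.

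Report the between-group difference in mean seconds per patient with a bootstrap 95% CI. With up to 65% zeros expected in the esketamine group, the median there may be 0 and say little. The rank test will also largely follow incidence, so the mean difference carries the information on time. Show duration among hypoxemic patients descriptively, without a test.

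Stratifying the test is optional. It would first require correcting the strata in Sequence generation {16a} (STOP-Bang 5–6 and ≥ 7), which leave out the eligible scores 3–4.

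The cost is one amended sentence, best made before anyone sees unblinded data. No new outcome is needed, but {18a} lists vital signs every 30 s and episodes over 10 s. The trial team should confirm that the full cumulative seconds that {12} already requires are being captured.

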##### Trial design {8}

This single-center, prospective, double-blind, randomized, superiority trial will evaluate whether low-dose esketamine (0.25 mg/kg) reduces hypoxemia incidence compared to placebo during propofol-sedated gastroscopy in patients with moderate-to-high OSA risk (STOP-Bang score ≥ 3).We will enroll 294 participants, randomly allocating them in a 1:1 ratio to either Esketamine group (0.25 mg/kg esketamine + propofol) or Control group (equal-volume saline + propofol). The study duration is 21 months. Eligible patients will be screened according to inclusion/exclusion criteria, with baseline characteristics recorded in case report forms (CRFs). Continuous monitoring of vital signs will occur from gastroscopy room admission through Post-Anesthesia Care Unit (PACU) recovery, with all interventions and assessments standardized (Fig. 1).

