## Data collection and management

### Plans for assessment and collection of outcomes {18a}

All outcomes will be systematically assessed, collected, and recorded on CRFs by blinded assessors across three phases: baseline demographics (age, sex, BMI), clinical characteristics (ASA status, STOP-Bang score, Difficulty in mask ventilation [DMV] risk factors), and room-air SpO_2_ will be collected pre-procedure; continuous vital signs (HR/SpO₂/NBP recorded every 30 s), propofol requirements, hypoxemia episodes (SpO_2_ < 90% > 10 s), procedure/recovery times, and adverse events (graded by blinded assessors) collected intraprocedure; Satisfaction (10-cm VAS), PACU recovery metrics (MOAA/S = 5 time), and AEs (graded 1–3 for severity/causality) collected post-procedure.

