### Methods in analysis to handle protocol non-adherence and any statistical methods to handle missing data {20c}

The primary analysis will follow the ITT principle, including all randomized participants regardless of adherence to maintain randomization benefits. Sensitivity analyses (per-protocol, as-treated, or instrumental variable methods) will assess robustness for major protocol deviations or treatment switches. Missing data will be addressed using multiple imputation or mixed-effects models under the missing-at-random assumption. Sensitivity analyses (worst-case imputation) will evaluate the impact of missing data, with explicit reporting of assumptions and comparisons between complete-case and imputed results.

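### Repeated measures ANOVA for MAP and HR can drop patients by procedure length; a baseline-adjusted mixed model in a stated window would avoid this

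*Protocol article*

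**What the plan says.** **Method.** Section {20a} of the protocol article (statistical methods for primary and secondary outcomes) fixes the analysis: MAP and HR over time "will be evaluated using repeated measures ANOVA". Post hoc Bonferroni corrections follow, with two-sided 0.05 for secondary outcomes. The section names no analysis time points and no baseline adjustment for this analysis.

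**Data.** Section {18a} (assessment and collection of outcomes) has heart rate, SpO2 and non-invasive blood pressure "recorded every 30 s" in the intraprocedure phase. Section {8} (trial design) adds: "Continuous monitoring of vital signs will occur from gastroscopy room admission through Post-Anesthesia Care Unit (PACU) recovery". Section {12} (outcomes) makes length of procedure a secondary outcome, and defines the baseline MAP used for hypotension as the mean of three pre-procedure readings. Section {10} (eligibility) makes a procedure longer than 15 min a withdrawal criterion.

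**Population and missing data.** Section {20a} has all randomised participants analysed by intention to treat. Section {20c} says: "Missing data will be addressed using multiple imputation or mixed-effects models under the missing-at-random assumption". Section {18b} (retention) instead gives mean imputation when less than 5% is missing.

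**The concern.** Classical repeated measures ANOVA works on a rectangle of patients by time points and deletes any patient with an empty cell. Here the number of intraprocedural readings differs from patient to patient because procedures end at different times. If the grid runs past the end of the shortest procedures, those patients leave the analysis because of something that happened after randomisation.

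Two things are at stake. The first is certain on such a grid: patients and precision are lost, and the analysis no longer covers everyone randomised. The second is conditional. If esketamine changes procedure length, and length goes with MAP or HR, the remaining patients in the two arms are no longer comparable. The protocol makes the first link plausible. Its discussion anticipates fewer involuntary movements, and section {12} includes movements that interrupt the procedure in that outcome.

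The abstract lists haemodynamic stability among the secondary outcomes, and the background names transient hypertension and tachycardia as possible effects of the drug. The outcome list in section {12} defines only hypotension. The MAP and HR trajectories are therefore where a rise would show.

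**Working it through.** The plan states no figure for this analysis, so there is none to reproduce. The check has four steps. Steps 2 and 3 rest on assumptions, because the documents give no distribution of procedure length.

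**1. Readings per patient.** One reading every 30 s is 2 per minute. At the 15-min limit that is 15 × 2 = 30 readings; a 5-min procedure gives 10. No intraprocedural grid is complete for everyone unless it stops at or before the shortest procedure.

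**2. Share of patients complete to grid end g.** Assume lognormal length with median m and log-SD s, restricted to 15 min or less. With F(x) = Φ(ln(x/m)/s), the share is [F(15) − F(g)] / F(15).

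Example, m = 5, s = 0.4, g = 10: F(10) = Φ(1.733) = 0.958 and F(15) = Φ(2.747) = 0.997, so the share is (0.997 − 0.958)/0.997 ≈ 0.04.

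Over m = 4 to 8 min and s = 0.3 to 0.5:

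| Grid end | Patients with complete readings |
|---|---|
| 2 min | 92–100% |
| 5 min | 23–94% |
| 10 min | 0.1–25% |
| 15 min | 0%, by construction (the limit itself) |

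**3. Bias in the complete-case MAP difference when the true difference is 0.** Assume m = 5 and s = 0.4. Let u be the standardised log length before any treatment effect, let MAP rise 4 mmHg per unit of u, and let esketamine shorten procedures by a fraction r. A control patient is complete if u > a₀ = ln(g/5)/0.4. An esketamine patient is complete if u > a₁ = a₀ − ln(1 − r)/0.4. Then

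bias = 4 × [λ(a₁) − λ(a₀)], where λ(a) = φ(a)/(1 − Φ(a)).

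Example, g = 5, r = 0.10: a₀ = 0, a₁ = 0.263, λ = 0.798 and 0.973, so bias = 4 × 0.175 = 0.70 mmHg.

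| Grid end | r = 0 | r = 10% | r = 20% |
|---|---|---|---|
| 2 min | 0 | 0.1 | 0.3 |
| 5 min | 0 | 0.7 | 1.5 |
| 8 min | 0 | 0.9 | 1.9 |

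If MAP is unrelated to length, the factor 4 becomes 0 and so does the bias, whatever r is.

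**4. The stated rules side by side.** Section {20a} names an ANOVA that needs complete rows and also promises analysis of all randomised participants. Section {20c} offers mixed-effects models, but as a missing-data device and without linking them to MAP and HR. Section {18b} gives mean imputation. None says whether an intraprocedural time point after the procedure has ended counts as missing. Such a value was never due, so a missing-at-random imputation has nothing to recover.

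**The case against.** The strongest reply is that the harmful grid is not in the plan. Section {18a} says how often signs are recorded, not which readings are levels of the ANOVA factor. The assessment schedule is a figure that is not shown, and an article may leave time points to an analysis plan. On a 2-min grid, or at event-anchored points such as post-induction, insertion, removal and PACU, few patients would be lost. This stands: the loss is conditional on the grid, and a reader who infers that the analysis will discard most patients goes further than the documents allow.

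Other stronger readings also fail.
- **That the comparison is biased.** This needs length to be related both to treatment and to MAP or HR, and the documents establish neither.
- **That no readings exist after scope removal.** Sections {8} and {12} plan monitoring and hypotension assessment into the PACU. Only intraprocedural readings stop with the procedure.
- **That Bonferroni sets every test at 0.05/30 = 0.0017.** That assumes 30 separate comparisons. The correction is described as post hoc, so it does not divide the overall group and group-by-time tests.
- **That closely spaced readings invalidate the ANOVA through non-sphericity.** Routine degrees-of-freedom corrections exist.

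A mixed model also has limits. An unstructured covariance over 30 points has 30 × 31/2 = 465 parameters for 294 patients, which is not workable. Under missing-at-random, the model implicitly extends trajectories past the end of short procedures unless the window is limited. Lack of baseline adjustment costs efficiency, not validity.

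What remains is that the article does fix the method, and that method tolerates no incomplete rows in data that will be incomplete on any but a short or event-anchored grid.

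**Conclusion.** The point holds as an improvement of minor to moderate importance. The named method is poorly suited to readings every 30 s over procedures of unequal length. On any intraprocedural grid longer than the shortest procedure it excludes patients by a post-randomisation outcome, against the intention-to-treat statement.

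Under the assumed lengths the loss runs from at most 8% of patients (2-min grid) to at least 75% (10-min grid). In the one bias scenario examined, the spurious MAP difference is 0.1 to 1.9 mmHg for a 10–20% shortening, and zero if either link is absent. These figures show how much the unstated grid matters; they do not predict this trial's result.

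The primary outcome, the sample size and the binary hypotension outcome do not depend on this analysis.

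**What to change.** In section {20a}, replace repeated measures ANOVA with a linear mixed model, fitted separately for MAP and HR.

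- **Readings:** all observed readings in a fixed early window, or at event-anchored points (for example post-induction, insertion, removal, PACU). State which.
- **Terms:** treatment, time, treatment-by-time, the pre-procedure baseline and the randomisation strata as actually used.
- **Covariance:** autoregressive, or unstructured only if there are few time points.
- **Contrast:** name one main treatment contrast, such as the mean difference over the window.
- **Missing data:** do not impute intraprocedural values beyond the end of the procedure, and reconcile sections {18b}, {20a} and {20c} so that one rule applies.

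The cost is analysis wording, slightly more analysis work and some reliance on the chosen covariance structure. The model runs in the SPSS version already named and needs no new data: a baseline MAP is already defined, and pre-procedure HR falls within the planned monitoring from room admission. The trial status section says recruitment is ongoing, so the change can be made before the final analysis.
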